## Abstract

**Background:**

Chemotherapy-induced peripheral neuropathy (CIPN) is a common and understudied consequence of taxane chemotherapy for breast cancer treatment. CIPN symptoms include numbness combined with tingling sensations, persistent shooting, stabbing, or burning pain even in the absence of painful stimuli, lower extremity muscle weakness, and impaired balance. CIPN symptoms often persist for a long time after completion of chemotherapy, causing significant loss of functional abilities and increased risk of falls. Persistent CIPN caused by taxanes represents a therapeutic challenge due to the limited treatment options. Resistance exercise has shown promising results; however, the effect of exercise on CIPN remains understudied. This study aims to assess the effects of exercise on gait, balance, and lower extremity muscle strength after a 16-week home-based exercise program compared to an educational attention control condition.

**Methods:**

A sample of 312 women who completed taxane-based chemotherapy for breast cancer and have symptomatic neuropathy is recruited from a community-dwelling sample. Participants are randomized to either a 16-week Home-Based Physical Activity Intervention or an Educational Attention control group. The home-based intervention protocol consists of targeted lower extremity stretches, followed by 10 min each of gait/balance and 10 min of resistive training accessed by hyperlink or DVD. An Exercise Diary records quantitative exercise data. The gait assessment includes temporospatial parameters and lower extremity joint angles using APDM motion sensors. Participants’ balance is assessed using the Sensory Organization Test (SOT) performed using a NeuroCom Balance Master. Isometric strength of hip, knee, and ankle flexor and extensor muscles is assessed using an isokinetic dynamometer, Biodex BX Advantage. In addition, we assess neuropathy symptoms using the FACT-Taxane Additional Concerns Subscale and nerve conduction velocity of the sural and peroneal nerve action potentials. Outcomes are assessed at baseline (prior to randomization) and 16 weeks.

**Discussion:**

There are currently no evidence-based interventions that address the functional declines associated with CIPN. If successful, this program is simple and easy to implement in the standard of care for individuals with CIPN. Gait and balance training have the potential to reduce physical dysfunction associated with CIPN and reduce the burden of disease in cancer survivors.

**Trial registration:**

ClinicalTrials.gov NCT04621721. Registered on August 3, 2020. ClincialTrials.gov is a primary registry of the World Health Organization International Clinical Trials Registry Platform (WHO ICTEP) network and includes all items from the WHO Trial Registration data set in Trial registration.

**Supplementary Information:**

The online version contains supplementary material available at 10.1186/s13063-022-06294-w.

## Introduction

### Background and rationale

Approximately 13% of women in the USA will develop invasive breast cancer throughout their lifetime. In 2021, it was estimated that 281,550 new cases of invasive breast cancer are expected to be diagnosed in women in the USA. The treatment of invasive breast cancer will require a chemotherapy regimen that includes taxanes as a standard treatment for invasive breast cancer [1]. Taxane-based chemotherapy can result in chemotherapy-induced peripheral neuropathy (CIPN) [1, 2]. CIPN includes numbness, tingling sensations, persistent shooting, stabbing, burning pain or loss of cutaneous sensation, lower extremity muscle weakness, and impaired balance [3, 4]. These symptoms are distributed distal to proximal, with the lower extremities being affected first. Chemotherapy-induced peripheral neuropathy can persist long after completion of chemotherapy, causing significant loss of functional abilities, compromising the quality of life, and increasing the risk of falls [4, 5]. Taxanes affect thick myelinated nerve fibers, resulting in muscle strength and position sense. Motor and sensory neuronal loss in the lower extremities results in weakness of large lower extremity muscle groups and reduced gait performance and ability to compensate for changes in terrain [6, 7]. Hypotonia from lower peripheral motor neuron and muscle involvement can result in an unsteady gait [8]. Persistent CIPN caused by taxanes represents a therapeutic challenge due to the limited treatment options.

Studies in animal models and humans have suggested that resistance exercise and balance training may offer the possibility of reducing the effects of peripheral neuropathy. Studies in animal models have shown that a treadmill exercise program before taxane administration and continuing over weeks prevented the development of peripheral neuropathy [9]. In addition, treadmill exercise upregulated protective neurotrophic factors that may be responsible for the neuroprotection achieved with exercise [10]. Recent randomized control trials (RCT) have found that exercise may reduce CIPN symptoms, especially in women with breast cancer [11, 12], and may help cancer survivors regulate inflammation through endogenous cytokine pathways [13]. In studies of individuals with chronic peripheral nerve disorders, short-term (6 and 12 weeks) home and community-based exercise programs increased average muscle strength, improved walk time, and significant improvements in activity limitation and overall health [14, 15]. The effects of exercise on CIPN caused by taxanes are promising and remain understudied. This randomized clinical trial (RCT) aims to assess the effects of exercise on gait, balance, and lower extremity muscle strength in 312 women randomized to either a 16-week home-based gait/balance intervention or an attention control educational cancer survivorship condition.

## Methods/design

### Study design

A two-group, 16-week randomized clinical trial is designed to address persistent taxane-induced peripheral neuropathy in women treated for invasive breast cancer. The study design is a parallel, two-arm, randomized controlled trial with a 1:1 ratio between groups.

A sample of 312 women who completed taxane-based chemotherapy for breast cancer and have symptomatic neuropathy (≥ 3 on a neuropathy visual analog scale VAS) ≥ 6 months following completion of taxane-based chemotherapy will be recruited. Participants are randomized to either a Home-Based Physical Activity Intervention (B-HAPI) for persistent taxane-induced neuropathy or an educational attention control group. Assessment of gait, balance, strength of lower extremity muscles, neuropathy symptoms, and nerve conduction velocity will be collected at baseline (prior to randomization) and 16 weeks. The participant flow diagram is shown in Fig. 1. The protocol follows the Standard Protocol Items: Recommendations for Interventional Trials (SPIRIT) Figure (Fig. 2) and Checklist (Additional File 1) [16].

**Fig. 1 Fig1:**
[figure not shown]
Participant flow diagram

**Fig. 2 Fig2:**
[figure not shown]
Schedule of enrolment, interventions, and assessments

### Study setting and recruitment

Assessment occurs at the Human Functional Performance Laboratory at the University of South Florida (HFPL). Community-dwelling breast cancer survivors are recruited from local breast cancer support groups, breast cancer clinics, local churches, and advertisements in local community papers. In addition, we use social media recruitment (multiple ads targeting different ages, race/ethnic groups), Facebook, Twitter, and Instagram. We distribute recruitment flyers at clinics, breast cancer support groups, and Hispanic and Black church outreach. Participants are considered for inclusion if they meet the criteria as defined below.

### Eligibility criteria

#### Primary inclusion criteria

Participants must meet the following criteria to be eligible for the study:
Female breast cancer survivor (≥ 21 years old).Have completed treatment (≥ 6 months) for invasive breast cancer with taxane-based chemotherapy.Have a peripheral neuropathy score of ≥ 3 by VAS rating.

#### Primary exclusion criteria

If the participants meet any of the following criteria during screening, they are not eligible for the study:
Have any disease (e.g., diabetes, human immunodeficiency virus) resulting in peripheral neuropathy or muscle weakness (chronic fatigue syndrome, multiple sclerosis, spinal cord tumors or injuries, stroke).Have any disease that would preclude exercise (preexisting cardiopulmonary disease, bone metastasis).Have symptomatic lymphedema or advanced disease at high risk for bone metastases and pathologic fracture.

#### Who will take the informed consent?

Participants who are 6 months or more post-treatment completion for non-metastatic breast cancer with taxane chemotherapy and who have a chemotherapy-induced peripheral neuropathy (CIPN) VAS score of ≥ 3 are screened for eligibility to participate in this study based on the criteria mentioned above. After the interested participant has been assessed as eligible, they are invited to the HFPL to discuss any remaining questions and sign the informed consent.

### Interventions

#### Intervention protocol

The Home-Based Physical Activity Intervention (B-HAPI) consists of a 16-week, home-based gait/balance training and progressive resistance exercises using resistance power bands for lower extremities. The exercise program contains detailed, easy-to-follow demonstrations for each gait/balance training and resistance exercise training led by a physical therapist. Each participant allocated to the intervention group receives an exercise plan, which is accessed via a link or DVD, demonstrating the correct performance of the exercises, and captures in a weekly Exercise Diary. In addition, all exercise sessions use an Exercise Diary to record quantitative exercise data. Intervention participants are instructed to perform the gait/balance and resistance exercises 3 days per week. The intervention group begins with a light warm-up and stretching activity at the beginning of the program, working into the 10 min each of gait/balance and 20 min of resistive (strength) training components. In addition, we conduct telephone follow-ups to assist in surmounting barriers to exercise. Tables 1 and 2 include the gait/balance training plan and resistance exercise program description.

**Table 1 Tab1:** Gait/balance training plan

Exercise	Time	Description
Walking forward and backward	30 s × 2	Two individuals stand facing each other, holding hands. As one person walks backward, the other walks forward.
Walking side to side head motion	30 s × 2	Stand straight, and walk forward, with the eyes focused straight ahead, turning the head from side to side every 5 steps, keeping a straight course and avoiding drifting.
Walking up/down head motion	30 s × 2	Stand straight, and walk forward, eyes straight ahead, and nod the head up and down approximately every 5 steps.
Static standing	1 min each	Performed on both a firm and thick foam surface. Stand with eyes open, shifting weight from right to left leg. Repeat with eyes closed.
Standing partial tandem	1 min each	Performed on both a firm and thick foam surface with eyes open and closed.
Tandem standing heel to toe	1 min each	Performed on both a firm and thick foam surface with eyes open and closed.
Standing with head turns	1 min each	Performed on both a firm and thick foam surface with anterior, posterior, and lateral foot positions.
Single leg stance	30 s each	Performed on firm surface, raise right leg, balancing as long as possible. Repeat with other leg.
March in place	30 s × 2	Performed on both a firm and thick foam surface, march in place slowly.

**Table 2 Tab2:** Resistance exercise program description

Resistance exercise	Muscle targeted	Exercise description
Calf raises	Gastrocnemius and soleus	Stand with their feet shoulder width apart and their knees fully extended and will push up on their toes as high as possible, keeping the torso erect.
Lunges	Gluteus maximus, hamstrings, quadriceps, and gastrocnemius	Standing with feet shoulder width apart, and hands on the hips. Take one step directly forward, keeping torso erect, and back knee slightly bent. With lead leg planted firmly in front, allow the lead hip and knee to slowly flex. Continue to flex until the trailing knee is only a few inches from the floor. Alternate legs and repeat.
Supine leg curls	Hamstring muscle group	Lie on the floor with legs bent to a 90° angle. Resistance band tubing is placed underneath the feet while the handles are placed one in each hand. Slowly, bring both heels away from the body until both legs are fully extended. Once fully extended, bring both feet back up toward the body until back in starting position.
Supine leg extensions	Abdominal and hip flexor muscles	Lying on the floor with legs bent to a 90° angle, feet flat on the floor. The resistance band tubing is placed under the foot, and the band handles with palms facing in. Extend the working knee from 90° until the leg is straightened. Slowly bring the extended leg back to the starting position. Repeat the set with the opposing leg.

#### Attention control protocol

Participants in the attention control group receive a journal to record their clinic appointments and standardized breast cancer survivorship education based upon information from the American Cancer Society. At each data collection encounter, the intervention research assistant discusses the information in each pamphlet, allowing time for questions related to the material. In addition, participants in the attention control group receive telephone calls every other week which entail a social visit and reminder of data collection/attention intervention appointments to equalize contact further.

### Criteria for discontinuing or modifying allocated interventions

Participants can leave the study for any reason if they wish to do so without consequences. The investigator can also end participation if the participant does not attend study visits. The patient data collected up to that moment will be included in the analysis.

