#### Intention to treat (ITT) approach

A full-information maximum likelihood approach for an intent-to-treat analysis is used, and a Monte Carlo simulation with 10,000 replications suggests we will be able to detect a minimum standardized effect of 0.30 with a probability of correctly rejecting a false null (power) of .81. If the recruitment rate is closer to 3 per week resulting in a sample of *N* = 468, the minimum detectable standardized effect is 0.25. By including additional control variables (all ES’s = .10), the minimum detectable effect sizes decrease to 0.27 and 0.22, respectively. A recent and relevant meta-analysis reported effect sizes for exercise intervention effects on similar outcomes ranging from ES = 0.30 to ES = 0.84 [30]. We will compare the mean differences between groups and the rates of change (slopes) between the groups.

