## Data collection, management, and analysis

### Assessment and collection of outcomes

The assessment of gait, balance, and lower extremity muscle strength is performed by personnel with Master of Science in Kinesiology trained to perform these assessments. In addition, the assessment of neuropathy symptoms patient-reported questionnaire and the nerve conduction velocity are performed by a member of the research team and a neurologist, respectively. Outcomes are collected at baseline and at 16 weeks to provide baseline and end of intervention data. These data collection points reflect current knowledge concerning the impact of exercise on gait, balance, and lower extremity muscle strength from pre- to post-intervention [31–34]. The outcomes assessment occurs at the Human Functional Performance Laboratory at the University of South Florida.

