### Data management

A codebook for all study variables is created. A trained research assistant enters data into SPSS, verified weekly. Data cleaning uses frequency counts for all variables at each data collection point to check for outliers. All possible strategies are employed to prevent missing data, including in-person data collection by trained research assistants. Missing data is considered analytically through full information maximum likelihood (FIML) procedures available in standard software for generalized mixed to reduce potential bias and loss of power that would otherwise occur when using traditional listwise deletion for missing data [42]. The codebook does not include paper case report forms (CRFs). Instead, we use the HIPPA-Compliant REDCap database as the electronic data capture for the study. We export the REDCap data or CSV files to be analyzed using SPSS and R for data analysis.

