### Data analysis

Univariate descriptive statistics will be used to describe the characteristics of the sample, gait, balance, and lower extremity muscle strength. Values for the exercise will be divided into quartiles to determine the uppermost and lowest values to compare with published literature [43]. Analysis of univariate statistics allows us to assess the normality of distributions for our continuously distributed variables, patterns of missing values, and whether univariate outliers may be present that could distort subsequent bivariate and multivariate analyses. By implementing appropriate link functions in the generalized linear model framework, distributional assumptions, such as normality and potential non-linearity, will be addressed. Potential non-normality may also be addressed by implementing robust estimation through Huber-White standard errors (i.e., “sandwich” estimators), also implementable in the generalized mixed model framework. We do not aggregate outcomes. Instead, we are looking at a specific change of each metric between baseline and 16 weeks and comparing study groups. In addition, we will perform baseline comparisons between groups. Any unbalance covariate(s) will be adjusted in multivariate analyses. We do not plan any subgroup analyses.

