#### Adverse event reporting

The risk to participants in this study is expected to be minimal. However, there is a small risk of falls in participants who experience gait and balance difficulties due to neuropathy resulting from taxane therapy. The study team advises safety precautions such as having a sturdy chair nearby and a person supervising the exercise to increase safety and minimize the risk of falls. Participants randomized to the exercise intervention may experience DOMS due to increased tension on muscle fibers during the first few exercise sessions. Exercise-related DOMS decreases with repeated stimuli and does not typically require medical attention. In addition, a breach of confidentiality is a potential risk. Study materials have unique study numbers and are kept secured in locked files to minimize the risk of a confidentiality breach.

Patients are interviewed at each visit for assessment and asked about any adverse events. Surveillance for adverse events (AEs) and other relevant clinical circumstances associated with study participation occur at in-person visits scheduled at 0 and 16 weeks using a standardized Adverse Event Record Form. Adverse event reporting is unmasked to the study statistician and Data Safety and Monitoring Board (DSMB). Any AE will be investigated immediately, assessed for relatedness and expectedness by the study PI, and reported in a timely fashion as required by the DSMB and University of South Florida IRB.

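### The rule for ending participation after missed visits provides for no later week-16 measurement, so it can add avoidable missing outcomes to an intention-to-treat analysis with one post-baseline assessment

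*Protocol article*

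**What the plan says.** The section Criteria for discontinuing or modifying allocated interventions lets women leave for any reason and adds: "The investigator can also end participation if the participant does not attend study visits". It continues: "The patient data collected up to that moment will be included in the analysis". It does not say which visits count, and it does not say that a woman whose participation has been ended is still invited to the week-16 assessment. Despite its heading, it does not separate stopping the program from stopping outcome collection.

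Assessment and collection of outcomes fixes the time points: "Outcomes are collected at baseline and at 16 weeks to provide baseline and end of intervention data". Data analysis names the quantity of interest: "we are looking at a specific change of each metric between baseline and 16 weeks and comparing study groups".

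The Intention to treat (ITT) approach section says: "A full-information maximum likelihood approach for an intent-to-treat analysis is used". Data management repeats the method and gives avoidance of listwise deletion as the reason: "Missing data is considered analytically through full information maximum likelihood (FIML) procedures". The SEM approach section plans for 312 women with 20% attrition and 10% periodic non-response.

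**The concern.** The trial has one post-baseline measurement. A woman who reaches the end of the trial without it has no outcome for any of the gait, balance or strength comparisons. A conduct rule that lets the team close her participation, and says nothing about measuring her later, therefore works against the intention-to-treat claim. Non-attendance may well be related to adherence or function, which is where missing at random is least secure. This is a stated rule of conduct and not a detail left to the statistical analysis plan. No analysis can recover an outcome that was never collected.

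**Working it through.** **1. When can the rule act?** The Adverse event reporting section says that surveillance visits "occur at in-person visits scheduled at 0 and 16 weeks". Table 3 shows no intermediate visit in either arm, only telephone calls. The Attention control protocol mentions a "reminder of data collection/attention intervention appointments", but the same section places the education at the data-collection encounters, so these are most naturally the same appointments. On this reading the only post-baseline visit that can be missed is week 16, and the rule allows participation to be closed at the point where rebooking could still yield the outcome. Removal before week 16 is possible only if other appointments count as study visits, which is unclear.

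**2. What does a baseline-only woman contribute?** The inputs from the SEM approach section are intercept variance 0.50, slope variance 0.10, covariance 0 and residual variance 0.50. Time is scored 0/1, which is an assumption.

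- Var(week 0) = 0.50 + 0.50 = 1.0
- Var(week 16) = 0.50 + 0.10 + 0.50 = 1.1
- Cov = 0.50
- Residual variance of week 16 given baseline = 1.1 − 0.50²/1.0 = 0.85

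In large samples, two-wave FIML with equal baseline means is equivalent to a baseline-adjusted comparison. Its precision on the treatment effect is set by n, the number measured at week 16: SE = √(4 × 0.85 / n).

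**3. The plan's own figure.** Power = Φ(0.30/SE − 1.96). The stated value is .81.

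| Measured at week 16 | n | Power |
|---|---|---|
| All | 312 | .82 |
| 20% lost | 312 × .8 = 250 | .73 |
| 20% then 10% lost | 312 × .8 × .9 = 225 | .68 |
| Half of the 20% recovered, then 10% lost | 312 × .9 × .9 = 253 | .73 |

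The stated .81 is matched only with no loss. The Mplus time scores and the scale of the 0.30 are not given, so this does not show the figure to be wrong, and the present point does not depend on it. The last row, about 28 more women and .05 more power, only illustrates what extra week-16 outcomes are worth. No passage says what share of attrition this rule would cause.

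**4. Does FIML repair the loss?** Data were simulated with the variances above: 312 women, a true effect of 0.30, about 20% missing at week 16 in each arm, and 4,000 replicates. The loss mechanisms are assumptions. In the last two rows with an effect of 0.30, women with lower values in the exercise arm are more likely to be lost.

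| Loss mechanism | Change among women measured | Week-16 score among women measured | FIML |
|---|---|---|---|
| Completely at random | 0.30 | 0.30 | 0.30 |
| Exercise-arm loss depends on baseline | 0.21 | 0.39 | 0.30 |
| Exercise-arm loss depends on the unseen week-16 value | 0.40 | 0.48 | 0.45 |

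With a true effect of zero, the last mechanism gives a FIML estimate of 0.15 and rejection in 26% of trials. FIML corrects loss that baseline explains. It does not correct loss that depends on the missing outcome.

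**The case against.** Several stronger readings are tempting, and the documents do not support them.

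- *Only data up to removal are kept.* The word only is not in the text. The sentence commits to retaining data.
- *The analysis becomes a completers analysis.* It does not. FIML is specified to avoid listwise deletion, and in the second simulated case it recovers 0.30 where the unadjusted comparisons of women measured give 0.21 or 0.39.
- *Women in the control arm can be removed early for missing attention appointments, so the rule acts differently by arm.* The contacts that differ by arm are telephone calls. The scheduled visits are the same in both arms.
- *The rule biases the result by up to a third of the target effect.* Such a figure multiplies an assumed gap between non-attenders and attenders by an assumed difference in loss, for example 0.5 SD × (30% − 10%) = 0.10 SD. It describes an unadjusted contrast and all attrition, and nothing ties either input to this rule.

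It is also fair to say that removal is discretionary, that nothing forbids rebooking, and that the protocol describes reminder calls and an intention to prevent missing data. Dependence on missing at random is common to any trial with dropout, and sensitivity analyses for it may be in the statistical analysis plan, which is not shown.

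What remains is narrower. The one explicit rule on non-attendance permits closing participation, and no passage says that such a woman is still to be measured at week 16.

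**Conclusion.** The point holds in this limited form. A woman whose participation is closed without a week-16 assessment stays in the likelihood but adds almost nothing to the treatment contrast. The intention-to-treat result then leans on the women measured at week 16 and on missing at random. In practice the main consequence is that a missed week-16 visit may be treated as final.

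The size cannot be derived from the documents, because the share of losses caused by this rule is not stated. The move from .68 to .73 in power assumes time scored 0/1, a baseline-adjusted model with residual variance 0.85, the two losses combined by multiplication, and recovery of half of the 20% attrition. The simulated bias shows what FIML cannot repair under an assumed mechanism and is not a forecast for this trial. The change is worth making because it is cheap and reduces avoidable missing primary outcomes.

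**What to change.** Replace the sentence on ending participation with a follow-up rule:

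- Missing a visit or stopping the allocated program does not end outcome follow-up.
- Every woman who has not withdrawn consent is invited to the week-16 laboratory assessment, within a rebooking window that the protocol states.
- The protocol says which appointments count as study visits.

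FACT-Taxane by telephone can be offered as an optional fallback. It rescues only that patient-reported outcome, since gait, balance and strength need the laboratory.

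This concerns outcome collection alone and leaves the rules on stopping the program as they are. The cost is one protocol amendment, rebooking calls and some late assessments. The Trial status section reports 33 women recruited at version 2, so 312 − 33 = 279 of the planned sample were still to come at that point.
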